## Background

Lumbar disc herniation (LDH) is one of the most common causes of nerve root pain, and become a painful, debilitating disorder in working adults [1]. In the majority of patients, experiencing their first episode of sciatica due to LDH, the symptoms recede to a non-disabling level within a period of six weeks [2].

LDH most typical symptoms are low back pain, accompanied by one or both lower extremity pain, numbness, pain, mostly by lumbosacral, buttocks, posterolateral to the lower limbs and feet, back radiation when bending, cough worse with movements. Herniated discs also often occur without symptoms, as revealed by magnetic resonance imaging studies in asymptomatic people. They are only clinically relevant when they impinge on a nerve root, causing radiculopathy [3,4].

In general, LDH is due to disc degeneration or trauma leading to nucleus, annulus fibrosis to the vertebral canal prominent, spinal cord or nerve root compression. As a result, conventional treatments including physical therapy, pain medication, anti-inflammatory drugs and surgery, are provided by physicians. Most patients with low back pain respond well to conservative therapy [5,6]. Recently, a large number of patients with LDH are turning to complementary and alternative treatments. Complementary and alternative treatments such as acupuncture are therefore attractive. Acupuncture is often used for LDH. For example, it is gaining popularity among LDH patients in the US and about 1 million consumers with musculoskeletal disorders utilize acupuncture annually [7].

Moxibustion is a traditional Chinese method that uses the heat generated by burning herbal preparations containing Artemisia vulgaris to stimulate acupoints [8]. Moxibustion has anti-inflammatory or immunomodulatory effects against chronic inflammatory conditions in humans [9,10]. Different moxibustion methods for treatment of LDH and their mechanism may be due to moxibustion can improve local blood circulation, eliminate nerve root inflammation and edema, loosen adhesions and improve protrusion and nerve root relations or the promotion of nerve injury repair [11,12]. Moreover, the heat of moxa treatment improves microcirculation in the lumbar vertebra.

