### Outcome

The improvement Japanese Orthopedic Association has proposed a series of criteria to define patient response in the context of clinical trials of LDH. M-JOA scale is known as the modified edition of JOA Back Pain Evaluation Questionnaire [23]. According to these criteria, a patient with LDH is assessed including pain, the activities of daily life and work, function impairment, and special exams (Table 1). This scoring system was previously validated [23]. The degree of LDH is divided into three levels: mild: < 10, moderate: 10 to 20, severe: > 20.

**Table 1 T1:** List of M-JOA

Item	Grade/Classification	Score
Subjective symptoms		
Lumbar and leg pain	No	0
	Mild pain or occasional moderate pain	1
	Usual moderate pain or occasional severe pain	2
	Frequent or continuous severe pain	3
Numbness	No	0
	Occasional	1
	Frequent but relief may be on their own	2
	Continuous, not alleviated	3
Objective signs		
Paravertebral tenderness	No	0
	Mild	1
	Moderate	2
	Severe	3
Myodynamia	Grade V	3
	Grade IV	2
	Grade III	1
	Grade 0 to II	0
Straight let raising test	> 70°, straight leg drive up (-)	0
	> 45°, straight leg drive up (+)	1
	> 30°, straight leg drive up (+)	2
	< 30°, straight leg drive up (+)	3
Radiating pain	No	0
	Hip/thigh	1
	Shank	2
	Foot	3
Activities of daily life and work		
Stoop and lift heavy things	Normal stoop, lift weight > 3 kg	0
	Able to stoop, lift weight ≤ 3 kg	1
	Unable to stoop	2
	Serious difficulties in bending and lifting	3
Walking distance/time	Walking ≥ 1 km or 60 min	0
	Walking ≥ 500 m or 30 min	1
	Walking ≥ 100 m or 10 min	2
	Serious difficulties in walking	3
Daily time in bed(h)	< 10	0
	10 to 12	1
	12 to 16	2
	> 16	3
Ability to work	Full-time to do as before	0
	Although able to work, occasionally need a break	1
	Although able to work, usually need a break	2
	Unable to work	3

Therapeutic effect is assessed by comparing baseline and final conditions reported by the patient. This trial also records adverse effects reported by patients during treatment. The outcome measures above will be assessed before treatment, the 14 days after the last moxibustion session and 6 months after the last moxibustion session.

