### Treatment protocol

#### Heat-sensitive moxibustion

Moxibustion will be performed by certified acupuncture medical doctors at four centers. Qualified specialists of acupuncture in traditional Chinese medicine with at least five years of clinical experience will perform the acupuncture in this study. All treatment regimens will be standardized between four centers practitioners via video, hands-on training and internet workshops. Participants will be randomly assigned to the heat-sensitive moxibustion group, the conventional moxibustion group. In the former groups, a 22 mm (diameter) × 120 mm (length) moxa-sticks (Jiangxi Traditional Chinese Medicine Hospital, China) will be used. The patient is usually in the comfortable supine position for treatment, with 24°C to 30°C temperature in the room.

For the heat-sensitive moxibustion group, the moxa-sticks are lit by the therapist and held over the region consisting in two Da Changshu (BL 25) and Yao Shu (Du 2) of patients. The warming suspended moxibustion about distance of 3 cm are used to search for the acupoint heat-sensitization phenomenon. The following patient sensation will suggest the special heat-sensitization aupoint: diathermanous sensation due to moxa-heat, defined as the heat sensation conducting from the moxa local skin surface into deep tissue; expand heat sensation due to moxa-heat, defined as the heat sensation spreading to the surrounding little by little around the moxa point; transfer heat sensation due to moxa-heat, defined as the heat sensation transferring along some pathway or direction. When some acupoint exists one below sensation at least, therapists mark the point as a heat-sensitive acupoint. We try our best to seek all the special acupoints in each patient by the repeated assessment.

The therapists begin to treat patients from the most heat-sensitive intensity acupoint. Treatment sessions end when patients feel the acupoint heat-sensitization phenomenon has disappeared. Generally speaking, we select one point each time. One point is treated 45 minutes. Patients receive the treatment for two times daily in the first four days and for one time daily in remaining ten days. The full treatment contains 18 sessions over 14 days.

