### Statistical methods

#### Statistical analysis plan

We will conduct analysis on an intention to treat basis, including all randomized participants. Analyses will be conducted using 2-sided significance tests at the 5% significance level. The analysis of center effect will be used logistic regression method. The statistician conducting the analyses will remain blind to treatment group and data will only be unblinded once all data summaries and analyses are completed. All analyses will be conducted in the SAS statistical package program (ver. 9.1.3).

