##### Follow-up data

The primary outcome will be the M-JOA scores. The primary analysis will compare the two groups at 14 days. A secondary analysis will compare the two groups at 6 months to assess if any differences between groups have been maintained over time.

Loss to follow-up is likely to lead to biased estimates of intervention effect. We will try to avoid bias due to attrition by carefully following up the participants in both groups. We will phone participants who do not complete questionnaires after a second reminder. We anticipate a 20% loss to follow-up in this trial, and will implement procedures to minimize loss to follow-up and patient withdrawal, and where possible we will collect information on reasons for patient withdrawal.

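### Both follow-up assessments are timed from the last moxibustion session rather than from randomisation, so early stoppers are measured sooner and never-treated patients have no assessment date

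*Protocol article*

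**What the plan says.** The Outcome section is the only place in the protocol article that anchors the post-baseline assessments. After the pre-treatment assessment they fall at "the 14 days after the last moxibustion session and 6 months after the last moxibustion session".

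The Follow-up data section names the endpoint, "The primary outcome will be the M-JOA scores", and the two comparisons: "The primary analysis will compare the two groups at 14 days" and "A secondary analysis will compare the two groups at 6 months". It gives no starting point for either interval, so it does not override the Outcome section. No section ties a visit to randomisation or to the first session.

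Both treatment sections plan the same course; for the heat-sensitive group the wording is "The full treatment contains 18 sessions over 14 days". On the analysis population, the Statistical analysis plan section says "We will conduct analysis on an intention to treat basis, including all randomized participants".

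**The concern.** The last session is a post-randomisation event, and its date depends on how long the patient stays on treatment. If visits are counted from it, the time between randomisation and the primary measurement becomes a function of adherence. A patient with no session has no starting point at all, which sits badly with an analysis of all randomised participants.

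Elapsed time may matter in this disease. The Objective section targets acute lumbar disc herniation. The Background says that in most patients with a first episode of sciatica "the symptoms recede to a non-disabling level within a period of six weeks". Day 28 lies inside six weeks if the patient enters near onset. Patients measured sooner have had less time to improve by themselves, whatever the treatment does.

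At stake is the comparability of the primary measurement across participants. If stopping is equally common and equally early in both arms, the result is extra variability. If it differs, part of the between-arm difference reflects the day of measurement.

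**Working it through.** **Inputs**
- Course, both arms: two sessions daily for the first four days, then one daily for ten days (both treatment sections).
- Assessments: last session + 14 days and + 6 months (Outcome).
- Population: all randomised (Statistical analysis plan section).
- Assumptions for the day count: day 1 is the first session and follows randomisation promptly; 6 months is taken as 182 days.

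**Plan's own figure.** 4 × 2 + 10 × 1 = 18 sessions over 4 + 10 = 14 days, which reproduces the stated course. A completer's last session is therefore on day 14.

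**Assessment dates.** Primary day = last-session day + 14; 6-month day = last-session day + 182.

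| Last session | Primary assessment | 6-month assessment | Days earlier than a completer |
|---|---|---|---|
| Day 14 | Day 28 | Day 196 | 0 |
| Day 10 | Day 24 | Day 192 | 4 |
| Day 7 | Day 21 | Day 189 | 7 |
| Day 4 | Day 18 | Day 186 | 10 |
| Day 1 | Day 15 | Day 183 | 13 |
| None | Undefined | Undefined | – |

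The largest shift is 13 days: 13/28 = 46% of the primary interval, but 13/196 = 6.6% of the 6-month interval.

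**Effect on the comparison.** For patients who stop early, a simple approximation is

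between-arm shift = r × e × δ,

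where r is spontaneous improvement in M-JOA points per day, e is the number of days measured early, and δ is the difference between arms in the proportion stopping early. With δ = 0 the shift is zero and only noise remains. The documents give none of r, e or δ, nor an SD, so the following is a range on assumed values, not an estimate.
- Assume a linear fall from a baseline of 15 to 25 down to 10 over 42 days, so r = (15 − 10)/42 = 0.12 to (25 − 10)/42 = 0.36 points per day.
- Assume e = 7 to 13 days. Per affected patient: (5/42) × 7 = 0.8 to (15/42) × 13 = 4.6 points.
- Assume δ = 5 to 20 percentage points. Between-arm shift: 0.83 × 0.05 = 0.04 to 4.64 × 0.20 = 0.93 points.
- Assume an SD of 4 to 6. Shift: 0.04/6 ≈ 0.01 SD to 0.93/4 = 0.23 SD.

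For scale, 126 per group at 90% power and two-sided 5% imply a standardised difference of √(2/126) × (1.960 + 1.282) = 0.41. The range is thus about 2% to 57% of that, and the upper end needs every assumption at its extreme. The range is too wide to support any single figure.

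**After anchoring on randomisation.** Every participant has the same target days (about 28 and 196), the spread in primary timing falls from 13 days to the width of the window, and the never-treated have a date. The sample size is unaffected: 126/0.80 = 157.5, rounded up to 158 per group, 316 in total, as stated.

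**The case against.** **The last session may mean the last scheduled one.** With a fixed course this is possible, and a condensed article may leave visit rules for early stoppers to the full protocol. But the article does state an anchor and does not call it scheduled. If the scheduled session is meant, saying so is essentially the change proposed below.

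**Does treatment stop earlier in the heat-sensitive arm?** A reader might infer this from "Treatment sessions end when patients feel the acupoint heat-sensitization phenomenon has disappeared", a rule given only for that arm. The documents do not support it. The sentence describes when a single session ends, and both arms have the same planned number of sessions over the same period. The article gives no reason to expect early stopping to differ by arm.

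**Can the bias be sized from the six-week recovery?** A reader might treat recovery as linear over 42 days and read off a spurious difference. The Background statement concerns first episodes and recovery to a non-disabling level. The eligibility criteria require neither a first episode nor a maximum duration, and the Baseline data section lists previous duration as a characteristic. Six weeks from trial entry is therefore not an established recovery period for these patients. This objection stands in full: spontaneous change is plausible, but its rate is unknown.

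**Never-treated patients are not dropped.** Correct: multiple imputation is planned, and participants who do not complete questionnaires will be phoned. Imputation supplies a score but does not define the date it refers to, and it would replace a measurement that could have been taken. How many such patients to expect is not stated.

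**An end-of-treatment anchor equalises time since treatment.** That is a legitimate aim. It stands as a cost of the change, but it serves an analysis of all randomised participants less well.

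**Conclusion.** The point holds as a cheap improvement to a stated rule. Taken literally, the Outcome section makes the time from randomisation to the primary assessment depend on treatment received, from about day 15 to about day 28 for patients who stop on or before schedule. It leaves the never-treated without a date in an analysis that is meant to include them. These dates assume only that treatment starts promptly after randomisation.

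The consequence is noise if early stopping is equal between arms and bias if it is not. Its size in M-JOA points cannot be derived from the documents. The concern is mainly the primary assessment; at 6 months the shift is minor. The documents do not show that differential stopping, or a biased result, is to be expected.

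**What to change.** Define both assessments as fixed days from randomisation, each with a window, for every randomised participant whatever treatment was received. For example, set the primary visit at day 28 and the later visit at 6 months after the scheduled end of the 14-day course (about day 196). Use the same definition in the Outcome and Follow-up data sections; at present the latter's 14 days could also be read as the end of the treatment period.

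The Design section's five sessions per week (10 in two weeks) should also be reconciled with the 18 sessions in the treatment sections, since the date of the last session depends on it.

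The cost is a wording amendment and a change in how visit dates are calculated. Sample size and treatment rules are untouched. Patients who start promptly and finish on schedule keep essentially the same dates; those who start or finish late have theirs moved slightly. Time since the last session will vary for early stoppers. If that interval is of interest, the last-session date can be recorded and described.

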### Design

A multi-center (four centers in China), randomized, subject blinded(group A and B) and assessor blinded, parallel positive controlled trial will be conducted at the affiliated Hospital of Jiangxi University of TCM in Nanchang, The first Affiliated Hospital of Anhui University of TCM in Hefei, Jiangsu TCM Hospital in Nanjing, and Shanxi TCM Hospital in Xian. The study will be sequentially conducted as follows: a recruitment period prior to randomization, a treatment period of 14 days (5 sessions per week), and a follow-up period of six months. Participants will be randomized to the heat-sensitive moxibustion group or the conventional moxibustion group by the central randomization system (Figure 1). This system is provided by China Academy of Chinese Medical Sciences, which adopted the computer telephone integration (CTI) technology to integrate computer, internet and telecom. The random number list will be assigned by interactive voice response (IVR) and interactive web response (IWR) [24]. The success of blinding will be assessed at each participant's last visit. Researchers who did not participate in the treatment and who are blinded to the allocation results will perform the outcome assessment. Patients meeting the inclusion criteria were randomly assigned in a 1:1 ratio to the two groups. We used the parallel controlled design and did not stratify by center or block within center.

**Figure 1 F1:**
[figure not shown]
**Test flow chart**.

### Eligibility

#### Inclusion criteria

Eligible participants will be those previously diagnosed with moderate to severe LDH, according to the M-JOA criteria(> 10 score). Patients will be required to complete the baseline LDH diary. Written informed consent will be obtained from each participant. Participants 18 to 65 years of age will be recruited from outpatient and inpatient in four centers. Standard of diagnosis listed as follows:

① Pain occurred in lower back and radiated to the lower limb; ② Limitations of tender point; ③ Straight leg raising test and it's strengthen test are positive; ④ Skin sensation, muscle strength and tendon reflex have some changes; Changes in spinal posture; ⑤ CT suggestive of disc herniation. The above standard mainly originated from the guiding principle of clinical research on new drugs (GPCRND) [23]. Since the research involves moderate to severe LDH or severe LDH, the inclusion criteria will restrict the following conditions: According to the below LDH diagnosis standard, meanwhile, the triangle region formed with bilateral Da Changshu (BL 25)and Yao Shu (Du 2) of patients (Da Changshu- Yao Shu -contralateral Da Changshu intra-region) appear heat-sensitive points.

Participants will be instructed to stop LDH symptomatic relief medication during the run-in and treatment periods and will be provided the usual care instruction for LDH.

Figure 1 The flow diagram is intended to depict the passage of participants through this RCT.

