**Discussion:**

The study design guarantees a high internal validity for the results. It is one large-scale randomized controlled trial to evaluate the efficacy of heat-sensitive moxibustion compared to conventional moxibustion and may provide evidence for this therapy as a treatment for moderate and severe lumbar disc herniation. Moreover, the result may uncover the inherent laws to improve the therapeutic effect with suspended moxibustion.

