#### Sample size

We wished to estimate the sample size that would suffice to detect M-JOA between the heat-sensitive and conventional moxibustion groups. If we apply a two-sided 5% significance level, 90% power the calculated required sample size is approximately 126 participants in each group, according to the equations in [26]. Allowing for a 20% loss to follow up, a total of 158 participants will be required in each group, with 316 participants in total.

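### The entry cut-off (M-JOA above 10) disagrees with the article's own moderate band (10 to 20) at a score of 10, and the reversed muscle-strength item in Table 1 distorts the same threshold

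*Protocol article*

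**What the plan says.** The Inclusion criteria section of the protocol article states the target severity and its numerical meaning together: patients must have moderate to severe disease "according to the M-JOA criteria(> 10 score"). The Outcome section, which introduces the scale, says: "The degree of LDH is divided into three levels: mild: < 10, moderate: 10 to 20, severe: > 20". The Discussion paragraph of the abstract names the same target population, saying that the trial "may provide evidence for this therapy as a treatment for moderate and severe lumbar disc herniation". A later sentence of the Inclusion criteria is less clear, "Since the research involves moderate to severe LDH or severe LDH, the inclusion criteria will restrict the following conditions", and gives no number.

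Table 1 in the Outcome section lists ten items, each scored 0 to 3. For nine of them the normal or symptom-free level scores 0. For Myodynamia, Grade V scores 3, Grade IV scores 2, Grade III scores 1 and Grade 0 to II scores 0.

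**The concern.** The inclusion criteria offer the cut-off as what the scale itself means by moderate to severe, not as a separate and narrower entry rule. The scale as printed puts 10 in the moderate band, so the criterion misstates the scale it relies on. The Outcome section uses strict inequalities at both ends (below 10, above 20), so it is natural to read the strict sign in the inclusion criteria literally too.

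The muscle-strength item bears on the same threshold. Higher totals mean worse disease, yet a patient with full strength collects 3 points and a markedly weak patient collects none. The total compared with the cut-off is then not a consistent measure of severity. What is at stake is who counts as eligible and how the enrolled population is described. The M-JOA score is also the primary outcome (Follow-up data section), so the direction of the item has to be known there as well.

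**Working it through.** **Background check on sample size.** The Sample size section gives 126 per group and 20% loss: 126 / (1 − 0.20) = 157.5, rounded up to 158 per group, and 2 × 158 = 316. This agrees with the article. The 126 itself cannot be rebuilt, because the article gives no effect size or standard deviation. No printed step of the calculation uses the entry cut-off.

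**Step 1: range of the total.** Ten items scored 0 to 3 give integer totals from 0 to 10 × 3 = 30, which is 31 values. A total of 10 is attainable.

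**Step 2: the two rules side by side.**

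| Total | Outcome section | Inclusion criteria |
|---|---|---|
| 0 to 9 | mild | not eligible |
| 10 | moderate | not eligible |
| 11 to 20 | moderate | eligible |
| 21 to 30 | severe | eligible |

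Moderate or severe covers 10 to 30 (21 values). Eligible covers 11 to 30 (20 values). They disagree at one value, 10, which is one of the 11 moderate values. If both sections used the same boundary, they would disagree at none.

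**Step 3: effect of the Myodynamia direction.** Let m be the printed item score and T the printed total. Running the item like the others replaces m by 3 − m, so the total becomes T + 3 − 2m.

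| Strength | m | Change in total | Effect near the cut-off |
|---|---|---|---|
| Grade V | 3 | −3 | 11 → 8, 12 → 9, 13 → 10 |
| Grade IV | 2 | −1 | 11 → 10 |
| Grade III | 1 | +1 | 9 → 10, 10 → 11 |
| Grade 0 to II | 0 | +3 | 7 → 10, 8 → 11, 9 → 12, 10 → 13 |

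With normal strength, printed totals of 11 and 12 pass the entry rule but would fall to 8 and 9, in the mild band. A printed 13 (Grade V) or 11 (Grade IV) would land on 10, the score on which the two sections disagree. Some weaker patients below the cut-off would move up to or over it. The last row may seldom arise, since the exclusion criteria rule out muscle paralysis from nerve palsy.

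**The case against.** The best reply is that the entry rule is clear in use. The Inclusion criteria give one explicit number, and the bands sit under Outcome, where a site would not look for an entry rule. Under that number a score of 10 is refused, and the mismatch amounts to a choice of inequality sign in a condensed article. Much of this stands, and it rules out several stronger readings that a reader might infer:

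- *The four centres will apply different rules.* Nothing in the article suggests that a site would set aside the printed cut-off and derive another from the Outcome section.
- *The enrolled population differs from the stated one.* On printed totals it lies wholly inside the stated population and lacks only its lowest score.
- *A number of the 316 patients is affected.* Applying an assumed share of candidates scoring 10 to the 316 randomized is not valid. If the inclusion criteria are followed, none of the 316 has a score of 10. Refused patients come from a screening pool of unknown size, and no score distribution is given.
- *The randomization system will enforce one version.* The Design section describes that system as assigning the random allocation and mentions no eligibility check in it.

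It can also be said that the muscle-strength item is a separate matter, since the conflict at 10 would remain if the item were reversed. That is correct as to cause. But both points act on the same threshold: reversing the item moves patients onto and across it, so settling one without the other leaves the threshold uncertain. Finally, the reversed scores may be a printing slip in the article and not in the form used at the centres. That is possible, which is why the item needs to be confirmed if it is not corrected.

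**Conclusion.** The contradiction is real, present in the current text and not resolved elsewhere in the article. It is minor: one integer score at the lower edge of the moderate band. Eligibility is decided before allocation, so both arms are affected alike and the comparison between them is not biased. The significance level, sample size and method of analysis are untouched.

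The reversed Myodynamia item widens the uncertainty about the threshold. Among admitted totals, only 11 and 12 with Grade V strength would become mild. This assumes that the table was applied as printed and that the item was meant to run in the same direction as the other nine. The article does not show which boundary was intended or whether the item direction was deliberate, and how many patients either point affects cannot be worked out from it. Any effect of the item direction on the outcome itself is not sized here.

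**What to change.** Reconcile the Outcome and Inclusion criteria sections so that the same boundary appears in both. Which boundary that should be is for the investigators to decide. Correct the direction of the Myodynamia item in Table 1, or confirm it with a reason, before the total is used for eligibility or as the outcome. The article reports a first randomization on 16 June 2011, so patients may already be enrolled. For them, recompute the baseline totals under the settled scoring and list any whose eligibility status changes.

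The boundary costs a one-line correction. The item costs a correction or a confirming note. If the forms were scored as printed and the direction is changed, baseline and outcome totals must also be recomputed. That is simple arithmetic if the item scores were kept (an assumption), and it needs no new data and no change to the sample size.
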